# Effects of a group mindfulness-based cognitive programme on smartphone addictive symptoms and resilience among adolescents: study protocol of a cluster-randomized controlled trial

**DOI:** 10.1186/s12912-021-00611-5

**Published:** 2021-06-05

**Keywords:** smartphone addiction, smartphone behavior, adolescents, mindfulness, cognitive therapy, cluster randomized controlled trial, nursing

## Abstract

**Background:**

Smartphone addiction in adolescent is a significant global health issue since the last decade. Evidence has shown that the uncontrolled use of smartphone would lead to undesirable impact on their growth and development. However, evidence-based interventions to manage adolescents’ smartphone addictive behaviors is lacking. The proposed study aims to examine the effect of a group mindfulness-based cognitive programme(MBCP) on resilience, smartphone behavior and addictive symptoms in young adolescents.

**Methods:**

It is an open-label, parallel-group, cluster-randomized controlled trial with repeated measurement analysis. Four primary schools in Hong Kong will be recruited and randomly allocated in a ratio of 1:1 to the intervention/control group. A convenience sample of 240 class level 5 primary school students, 60 from each school, will be recruited. Participants in the intervention group will receive a 12-week MBCP which comprises 90-minute supervised practice at school and daily home practice. Resilience will be measured by Connor-Davidson Resilience Scale – 25 (Chinese version); smartphone behavior will be represented by time spent/day using the smartphone and types of functions used; addictive symptoms will be measured by Smartphone Addiction Scale-Short Version (Chinese Version). Baseline assessment(T0) will be conducted before the intervention starts. Post-tests will be conducted in weeks 4, 8, 12 of the intervention, and 3 months follow-up. Intention-to-Treat analysis will be applied to the variables. Generalized Estimating Equation model will be used to compare differences in resilience scores, smartphone behavior and addiction scores between and within groups, adjusted for socio-demographic factors. *P* < 0.05 with two-tailed test will be regarded as significance.

**Discussion:**

It is expected that adolescents will demonstrate better resilience and lesser smartphone addictive symptoms after joining the MBCP. The study will be the first provided empirical evidence to support the promising application of MBCP to manage smartphone use among adolescents. It introduces community stakeholders including community nurses a non-invasive and simple-to-administer intervention to tackle problematic smartphone use among adolescent clients.

**Trial registration:**

Chinese Clinical Trial Registry, ChiCTR2000033273, Registered on 26 May 2020.

## Background

The smartphone has become indispensable in the lives of most of humankind during the last two decades [1, 2]. More than 75 % of families own mobile devices such as smartphones [3]. Recent statistics from local and national surveys reveal a rapidly increasing trend in the use and possession of smartphones not only among adults but also among children and adolescents [4]. In 2011, 52 % of children below 9 years of age had access to mobile devices; in 2013, that access rate had increased to 75 % [5]. In 2018, about half of the elementary school students in the United State and Europe, possessed their own mobile phone [6]. In 2009, the average screen time of 8- to 18-year-old youngsters was 7.38 h, which is 1.17 h more than the one reported in 1999 [7]. A similar pattern has been observed in Hong Kong. A survey about the use of smartphones among 10- to 24-year-old adolescents and young adults revealed that 88.8 % of the respondents possessed a smartphone [8]. The older the age, the higher the possession rate [1]. The average time spent on screen media increased 15 % in nine years’ time, from 2003 to 2012. In particular, young adolescents aged 10 to 14 years showed the largest increase in screen time. Their average duration spent on screen media per week increased from 14.6 h to 2003 to 18.5 h in 2013 (an increase of nearly 27 %) [4].

The continuously increasing possession and use of mobile devices among children and adolescents is alarming because both their bodies and minds have not yet fully developed; in particular, their self-discipline is weak. The uncontrolled use of these mobile devices will make them even more susceptible than adults to the negative effects of mobile devices on their physio-psycho-social health [1]. Preliminary evidence shows that prolonged engagement with these devices disrupts cognitive development and leads to various physiological and psychosocial problems, including but not limited to visual problems, disruptions of memory, decline of attention, addiction, learning and social problems [1, 9, 10]. Furthermore, breaking addictive patterns early in life will help them maintain the benefits into adulthood. The research team therefore focuses on investigating effective intervention to manage the addictive smartphone behavior of this vulnerable group.

Smartphone behavior includes the daily duration and frequency of smartphone use and types of functions used. The findings among studies about the pattern of using smartphone in adolescents vary with the countries of origin and target groups [9]. Social networking is one of the popular smartphone functions being used most by adolescents and adults [11–15]. Some evidence shows that adolescents using smartphones for social networking are more likely to become smartphone addicts [11, 15]. Watching television content online with a smartphone is popular among younger children in Europe and the United States [14, 16]. Other activities such as seeking information, completing homework and killing time are common reasons youngsters stay online [1, 8, 16, 17]. Department of Health (2018) conducted a focus group interview to explore the views of using the internet and electronic screen products among school students in Hong Kong [1]. It showed that playing games was a major activity to relieve students’ stress created by heavy homework. Van Deursen et al. (2015) reported that both process- and social-related gratifications were associated with addictive smartphone behaviors in adults [15].

Uncontrollable use of smartphone is problematic and will lead to addiction to the smartphone use in the worst cases. Smartphone addiction is being perceived as a unique type of behavioral addiction distinguished from internet addiction [18]. The smartphone is a portable electronic device which has the functions of a telephone as well as the capabilities of a computer. It can be used for communication; for internet-based activities; and for personal purposes through the many “apps” available [11, 19]. Symptoms of smartphone addiction are (1) smartphone is his companion, on which he/she relies to can produce pleasure and relieve stress; (2) a person is unable to control his use of the smartphone, particularly for engaging with social media, etc.; and (3) the uncontrolled use has negative effects on his/her financial, physical, psychological and social aspects [20, 21]. Park et al. (2018) reported that about 11 % of South Korean adolescents were at high risk of smartphone addiction which required further assessment and intervention [22]. Haug et al. (2015) found that 17 % of adolescents and young adults in Switzerland were addicted to smartphone [11]. In Hong Kong, 19–27 % of 11- to 18-year-old adolescents were found to be either at risk of internet addiction or were confirmed internet addicts (Shek et al., 2008; Shek & Yu, 2012) [23, 24]. Some studies showed that gender, age, family characteristics are significantly associated with smartphone addiction [15, 22, 25].

A growing body of evidence demonstrated that such smartphone addiction is associated with numerous problems in physical, psychological and social health of children and adolescents. Excessive smartphone use is found to be associated with poor sleep quality, cardiovascular risk factors, attention-deficit hyperactivity, and depression and anxiety symptoms [26–28]. It is also shown that smartphone addiction is associated with behavioral and sexual issues commonly identified in adolescents such as antisocial behaviors, smoking, alcohol consumption, more sexually active [27, 29, 30]. The significant linkage of smartphone addiction with a wide range of physio-psychosocial problems among adolescents urges nurses especially those working school and other youth health care settings to look for effective preventive measures to tackle the uncontrollable smartphone use among adolescents prior to the occurrences of negative heath consequences.

### Resilience as a potential protective factor for smartphone addiction

Previous observational studies showed that psychological traits such as resilience may better predict smartphone addition than the pattern of smartphone behavior [31, 32]. Resilience is one’s ability to maintain psychological wellbeing and adapt to stress or difficult situations successfully [33, 34]. Factors affecting resilience development include intrinsic characteristics of an individual such as strong emotion regulation, high coping self-efficacy; child’s relationships with parents and social factors such as quality of schools and neighborhoods [35]. Low resilience has been found to be associated with internet/smartphone addiction. Strong resilience was found to be a key factor in protecting adolescents from experiencing online risks. It can also neutralize the negative psychological effects associated with internet addiction and online risk exposure [36]. 9–10 year-old youngsters with low resilience had a higher risk of becoming internet addicts [37–39]. Kim et al. (2014) examined the association of depression, impulsiveness and resilience on smartphone addiction in university students in South Korea. It reported that the addiction group spent more time using smartphones on weekdays than the non-addiction group. The addiction group had a significantly lower resilience score measured by Conner-Davidson Resilience Scale than the non-addiction group [27]. Jung and Kim (2015) found that adolescents with high addiction risk had a significantly lower ego resilience than those with potential or no risk [40]. More recent studies showed that resilience have a mediating effect on smartphone dependency and depression and aggressiveness among adolescents though the mediating effects may be different between sexes in internet addiction [32, 41–43]. The current evidence suggests that resilience can play a role in modulating addictive behavior of smartphone users. Increasing one’s resilience may help to prevent the addiction. It implicates nurses to look for evidence-based intervention to strengthen resilience to minimize health issues associated with smartphone addiction.

### Mindfulness-Based Cognitive Therapy (MBCT)

Little research has been conducted so far regarding effective management of smartphone addiction [44]. It is proposed that a person’s subconscious addictive behavior may be corrected by [45, 46]. Mindfulness is a kind of meditation originating from Buddhist practice. It aims to engage an individual in a full, direct, active and continuous awareness of experienced phenomena [46]. Available evidence supports that practicing mindfulness during childhood and adolescence may facilitate healthy psychosocial development such as strengthening executive function, increasing affective self-regulation, increasing the ability to moderate strong emotional states, and improving interpersonal relationships [47–50]. Studies investigating the role of mindfulness in managing behavioral addiction have primarily focused on problem gambling and work addiction, and they have rarely targeted children and/or adolescents [45]. The effect of mindfulness on smartphone addiction is yet to be explored [51]. Nonetheless, strong emotion regulation is one of prominent psychosocial characteristics of resilience [35]. Enhancing adolescents’ emotion regulation through mindfulness-related activities may possibly help to increase their resilience and so to modulate the smartphone behavior. Lee et al. (2008) developed a mindfulness-based cognitive therapy for 8- to 12-year-old children (MBCT-C) based on the adult MBCT developed by Segal et al. (2002) [52, 53]. It was intended to increase social-emotional resilience through strengthening mindful attention of children with anxiety problems [54]. A pilot study conducted by Lee et al. (2008) showed that the MBCT-C was feasible with children and that it could relieve their attention and anxiety problems [52]. Semple et al. (2010) conducted a randomized controlled trial to evaluate MBCT-C on 25 children aged 9 to 12 years [54]. Consistent trends of reduced anxiety and depressive symptoms were observed for the participants completing a full course of the therapy. In addition, 61 % of the parents reported that fewer conduct or anger management problems were observed on their children after participating in the programme. Although the small sample size may compromise the validity of these findings, it suggests the potential of MCBT-C to manage children with emotional and behavioral problems. As such, the research team will apply this therapy with adolescents and evaluate its effect on their resilience, smartphone behavior and smartphone addictive symptoms. This research protocol presents the design of this study and discuss the potential nursing implication of the study findings.

## Methods/Design

### Aim/Objectives

The aim of this study is to examine, through a cluster randomized controlled trial, the effects of a group mindfulness-based cognitive programme on smartphone behavior, resilience and symptoms of smartphone addiction in adolescents.

The primary objective is to investigate the group by the time interaction effects of the group mindfulness-based cognitive programme on resilience, smartphone behavior and the symptoms of smartphone addiction in adolescents.

There are two secondary objectives: (1) To identify adolescents with smartphone addictive symptoms using the Smartphone Addiction Scale-Short Version; (2) To investigate the association of socio-demographic factors, smartphone behavior and resilience with smartphone addiction symptoms in adolescents.

### Hypotheses

The three primary hypotheses of this study are: (1) the smartphone behavior of adolescents can be improved by participating in a group mindfulness-based cognitive programme; (2) the smartphone addictive symptoms of adolescents can be reduced by participating in a group mindfulness-based cognitive programme; (3) the resilience of adolescents can be increased by participating in a group mindfulness-based cognitive programme. The secondary hypothesis is that socio-demographic characteristics, resilience and smartphone behavior are associated with the symptoms of smartphone addiction in adolescents.

### Study design and setting

This study will be an open-label, parallel-group, cluster randomized controlled trial with repeated measurement analysis. It will pragmatically evaluate the effects of the mindfulness-based cognitive programme (MBCP) on improving adolescents’ resilience, changing their smartphone behavior and reducing smartphone addictive symptoms as compared with the control group at five measurement points (i.e. baseline (T0), one month (T1), two months (T2), three months (T3) after the programme, three months’ follow up (T4)). The study will be conducted in four primary schools in Hong Kong. The primary schools will be the unit of allocation, and individual participants will be the units of analysis. The intervention group will receive the mindfulness-based programme, and the control group will receive existing counselling services for students with emotional/behavioral problems. (i.e. treatment as usual). Data collection will be started in September 2020. Key aspects of the study design can be found in Fig. 1. We designed and reported this study protocol according to the SPIRIT2013 statement.

**Fig. 1 Fig1:**
[figure not shown]
Standard Protocol Items: Recommendations for Interventional Trials (SPIRIT) Figure

### School and participant recruitment

Primary school will be the cluster for randomization. Four primary schools in Hong Kong will be recruited based on their eligibility and willingness to participate in the study. The inclusion criteria for school selection are: (1) it is either a local government-subsidized or a private primary school; and (2) there are currently no interventions adopted by the school to manage students’ smartphone behavior. The exclusion criteria are (1) it is an international school; and (2) there are currently interventions being implemented by the school to manage students’ smartphone behavior.

A convenience sample of 240 students will then be recruited from the selected schools (i.e., 60 students from each school) based on their eligibility and consent to participate. The inclusion criteria are: (1) adolescents are aged 10–11 years; (2) adolescents are enrolling in class level 5; (3) adolescents possess a smartphone or can access a smartphone; (4) adolescents can speak, understand and write Cantonese; (5) adolescents are cognitively capable of following simple instructions. Adolescents have intellectual/learning disabilities will be excluded from the selection.

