### Randomization and blinding

The four participating schools will be cluster-randomized at a ratio of 1:1 into the intervention and control groups by coin toss by the research assistant A (RA-A) who will not be involved in participant recruitment and data collection. All students recruited under the same participating school were exposed to the same intervention. The principal investigator, who will be responsible for recruiting the schools and the students, will code the participating schools with a number and a letter to represent the district and the school, respectively. RA-A will only know the four codes but not the names of the schools. The school will be assigned to the intervention group if the landed side is heads; the school will be assigned to the control group if the landed side is tails. The allocation result will be kept by the RA-A in a sealed opaque envelope until participant recruitment. The school teachers, parents and students will not be informed of the research hypotheses. RA-A will feed data into the computer in separate datasheets so that the co-investigator responsible for data analysis can analyze data without having access to information about the allocation. Hence, it is a single-blind design.

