### Data analysis

IBM SPSS version 23 will be used for statistical analysis. Mean and standard deviation will be reported for continuous variables, i.e. age, types of smartphone functions used and total resilience score. Frequency and percentage will be reported for nominal and ordinal variables. Cronbach’s alpha and intra-class correlation coefficients will be calculated to determine the validities and reliabilities of the two scales: the translated Smartphone Addiction Scale and the Chinese Version of Conner-Davidson Resilience Scale – 25. Independent t-test/Mann-Whitney U test will be used to compare the socio-demographic variables between intervention and control groups. Generalized Estimating Equation model will be used to verify all the hypotheses. The socio-demographic variables will be treated as co-variates to adjust the group means. Results will be reported with 95 % confidence interval. Intention-to-treat analyses will be applied to the independent and dependent variables. Missing data will be handled by replacing the missing values with the item-specific mean. Tests performed will be two-tailed with alpha value set at 0.05. Cohen’s *d*, calculated by taking the difference of the adjusted means between two comparison groups and dividing it by the pooled standard deviation, will be used to estimate the effect size of the treatment.

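### Two school types are eligible and four schools are tossed separately, so school type can by chance coincide with arm; pairing schools before the toss prevents this at little cost

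*Protocol article*

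**What the plan says.** Under School and participant recruitment, a school qualifies if "it is either a local government-subsidized or a private primary school"; international schools and schools already running a smartphone intervention are excluded. "Four primary schools in Hong Kong will be recruited based on their eligibility and willingness to participate in the study". No rule sets how many of each type there will be.

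Under Randomization and blinding, "The four participating schools will be cluster-randomized at a ratio of 1:1 into the intervention and control groups by coin toss". The toss is described school by school: "The school will be assigned to the intervention group if the landed side is heads", and to control on tails. No pairs, strata or other constraint are mentioned. The principal investigator "will code the participating schools with a number and a letter to represent the district and the school, respectively", so the allocator's code carries district but not school type.

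Under Data analysis, "The socio-demographic variables will be treated as co-variates to adjust the group means". The Demographics list holds only pupil and family items: sex, age, parental education and employment, family structure and parenting skills. The limitations paragraph of the Discussion concedes that only four schools may bias the results and relies on the GEE model for the clustering.

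**The concern.** The Background gives reasons to expect schools to differ on the outcomes. It counts "social factors such as quality of schools and neighborhoods" among the influences on resilience, and says that "gender, age, family characteristics are significantly associated with smartphone addiction". Subsidised and private schools may plausibly draw on different families and neighbourhoods.

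With four clusters, chance cannot be relied on to balance a school-level characteristic. If both private schools land in one arm, school type and treatment are the same variable. Adding type as a covariate does not help, because it is collinear with arm. GEE does not help either: it accounts for correlation within schools, not for a mean difference between types that lines up with the arms. A difference between types in how resilience or smartphone use changes over the study would then be read as the programme's effect, or would hide it.

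**Working it through.** **Inputs.** Four schools of 60 pupils, 120 per arm, d = 0.5, ICC 0.01, 20% dropout, type I error 0.05, type II error 0.2 (Sample size calculation); two-tailed tests (Data analysis); 1:1 by coin toss (Randomization and blinding). The number of private schools is not given, so 0 to 4 are all considered.

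**The protocol's own figure.** Without clustering, n per arm = 2(1.96 + 0.84)² / 0.5² = 63 (64 by the t-test). With 60 × 0.8 = 48 completers per school, the design effect is 1 + 47 × 0.01 = 1.47. Then 63 × 1.47 gives 93 and 93 / 0.8 gives 117 per arm, or 234 in total; starting from 64 gives 238. Both are close to the stated 240, so the ICC of 0.01 is the value in use.

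**Exact 2:2 allocation.** There are C(4,2) = 6 allocations, taken as equally likely. The gap is the absolute difference between arms in the proportion of private schools.

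| Private schools | Allocations by gap |
|---|---|
| 0 or 4 | 6 of 6: gap 0 |
| 1 or 3 | 6 of 6: gap 0.5 |
| 2 | 2 of 6 (33%): gap 1; 4 of 6: gap 0 |

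Full confounding under 2:2 therefore needs exactly two private schools.

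**Four independent tosses, as literally described.** There are 2⁴ = 16 sequences. In a 2+2 mix:
- 4 are balanced 2:2 splits;
- 2 are fully confounded 2:2 splits;
- 8 are 3:1 or 1:3 splits with a 67-point gap;
- 2 leave an arm empty.

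Whatever the mix, only 6 of 16 sequences give two schools per arm. With one private school, 2 of 16 place it alone in an arm, which is also full confounding.

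**What enters the estimate.** If the two types differ by δ in change from baseline, the contribution to the group-by-time contrast is δ × (signed gap): δ in full when the gap is 1, δ/2 when it is 0.5. Averaged over the six allocations it is zero (2+2 mix: +1, −1 and four zeros; 3:1 mix: three at +0.5 and three at −0.5).

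**Possible size.** The protocol gives no value for δ. As a guide only, assume that in a 2+2 mix type explains all between-school variance in level. Two schools lie at +a and two at −a, so a² = ICC (in units of total variance) and the gap between types is 2√ICC.

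| ICC | Gap in level (SD) | Share of d = 0.5 |
|---|---|---|
| 0.01 (protocol) | 0.20 | 40% |
| 0.02 (assumed) | 0.28 | 57% |
| 0.05 (assumed) | 0.45 | 89% |
| 0.10 (assumed) | 0.63 | 126% |

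These are gaps in level, not in change.

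**With one toss per same-type pair (2+2 mix).** There are 2 × 2 = 4 allocations, all 2:2 and all with gap 0.

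**The case against.** The strongest reply is that the problem is conditional at every step. The protocol allows a mix of school types without saying there will be one, and full confounding under 2:2 needs one particular mix and then one third of the allocations. That stands, and 33% must be read as conditional on a 2+2 mix.

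Second, the cited background concerns levels of resilience and addiction, whereas the primary objective is a group-by-time effect with a T0 baseline. A constant difference between types drops out of that contrast, and parental education and employment are partial proxies for type. This also stands: only a type difference in change remains, and nothing in the protocol shows that one exists. One caveat is that Cohen's d is defined from adjusted means with only socio-demographic covariates named, so whether it has the same protection depends on detail the article does not give.

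Third, randomisation remains unbiased on average, as the zero mean above shows, and the limitations paragraph already admits the risk of having four schools. That is correct, but admitting a risk is no reason to leave an avoidable part of it in the allocation.

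Fourth, pairing has a price. A school-level analysis that respects two pairs has 1 degree of freedom instead of 2 (two-sided 5% critical value 12.71 against 4.30), and the smallest two-sided permutation p-value rises from 2/6 to 2/4. This is true, but the planned analysis is an individual-level GEE, and neither permutation value comes near 0.05.

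A reader might also infer that the comparison is confounded beyond repair whatever happens, or that single-sex schools add a further layer. The documents support neither. Inseparability is confined to the fully confounded allocations. Single-sex schools are nowhere mentioned, and pupil sex is already a covariate.

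**Conclusion.** The concern holds as an avoidable risk in the allocation, not as an error in the eligibility criteria. In a 2+2 mix with exact 2:2 allocation there is a 33% chance that school type equals arm, and a type difference in change then cannot be separated from the programme effect. In a 3:1 mix every 2:2 allocation carries a 50-point gap and half of any such difference. With one type there is no issue. The result assumes equally likely allocations and rests on a recruitment mix that the protocol leaves open.

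The size of any distortion is unknown. The 0.20 to 0.63 SD range depends on the extreme assumption that type explains all between-school variance, and it describes level. It shows that the matter need not be trivial beside d = 0.5; it does not estimate a bias. The remedy costs little, so the improvement is worth making.

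**What to change.** In Randomization and blinding, replace the toss for each school with a toss for each pair. After the four schools are recruited and before allocation, the principal investigator forms two pairs of the most similar schools, by school type first and then by the district already in the code. Research assistant A, who still sees only codes, tosses once per pair: heads sends the first-coded school to the programme and the second to control; tails does the reverse. Report school type by arm and keep the planned GEE.

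In a 2+2 mix this removes full confounding (33% to 0%). In any mix it guarantees the stated 1:1 split. It cannot balance a 3:1 mix, because three schools of one type and one of the other never make two same-type pairs; the remaining 50-point gap should then be stated as a limitation.

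The cost is a change of wording, a fall in possible allocations from six to four, and the loss of one of two degrees of freedom in any school-level analysis that respects the pairs. The sample of 240 does not change. Limiting eligibility to one school type would also remove the imbalance, but it narrows applicability and is optional.
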